## Materials and Equipment

### Participants

The number of participants needed when conducting the study according to this protocol mostly depends on the desired effect size we would like to be able to detect and the statistical power we would like to achieve. For example, using the multivariate analysis of variance, if we would like to achieve a power of at least 1−β = 0.90 to detect small effects (*f*^2^ = 0.02) with the probability of *Type I* error set at α = 0.05, we would need a sample size of *N* = 439 as calculated using *G^∗^Power 3* (Faul et al., 2007). However, given that it is expected that researchers will have to omit some participants whose scores do not meet the criteria for individualizing and binding groupings which will be determined from the data [due to calls-to-action not being (in)congruent enough with their moral views], it would be advisable to further increase the number of participants by 20%. Therefore, the ideal final sample would be around *N* = 527. Of course, if one would, for example, like to study the effects of (in)congruent calls-to-action and norms on donations to two different charity causes separately (e.g., those hypothesized to be more in line with liberals’ and conservatives’ values), one would need to double this number. On the other hand, if one is willing to the accept somewhat lower power of 1−β = 0.80, that is usually accepted in psychological research, one would need the sample size of *N* = 344, or around *N* = 412 if one decides to increase it by 20%.

The recruitment of participants can take place online. For example, in order to obtain a mixture of conservative and liberal participants, the link to the survey can be disseminated through different conservatively and liberally oriented Facebook groups (see Table A1 in Appendix A). Other online platforms where it is relatively easy to approach the users of different ideological positions can be also utilized, such as Reddit, Twitter etc.

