## Stepwise Procedure

This experimental study uses a 3 (morally (in)congruent/neutral calls-to-action) × 2 (presence/absence of social norm) between-subjects design and can be conducted online through a custom developed app or existing survey platform. The study procedure can be split into eight steps. (1) Firstly, participants receive a brief description of the study and its goals (e.g., “we want to explore the relationship between morality and CB and test the effectiveness of appeals to donate”) and are asked to provide informed consent for participation. (2) Secondly, participants complete the MFQ and the Moral Internalization subscale. (3) Thirdly, participants are asked to complete a basic demographic questionnaire. (4) Thereafter, the participants are randomly assigned to one of the two different charity causes and to one of six different experimental conditions. We use random assignment to ensure that samples are similar across conditions in terms of observed and unobserved characteristics. After the experimental exposure, participants are first asked about their attitudes toward charitable behavior and perception of social norms regarding the CB (5) and are then asked to indicate their willingness to donate (a) time and (b) money to the charity they were presented (6). The sequence of presenting the questions to donate time versus money will vary randomly in order to minimize the potential influence of sequence on both donation measures. Next, the participants are provided with a feedback regarding their scores on the MFQ and moral identity internalization questionnaire (7). Finally, an optional step is asking permission to collect participants’ Facebook data. Participants can either accept or deny this request. Regardless of their choice, in the last step, debriefing about the study and contact for further inquiries are provided (8). See Figure 2 for a visualization of this procedure.

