## Statistical Analysis

To test for the effects of moral congruence of the calls-to-action, descriptive social norms, and their interaction on donations of time and money, a multivariate analysis of variance (MANOVA) will be conducted. In the same analysis, a test for the moderating effect of moral internalization on the congruence of the calls-to-action will also be conducted. This approach allows researchers to account for potential relationships between our dependent variables, and to test whether the experimental manipulations influence participants on a combination of different types of donations (Field, 2009). Furthermore, in comparison with univariate ANOVA, that requires several individual tests, using MANOVA reduces the probability of making a *Type I* error.

To test whether attitudes toward CB mediate the effects of (in)congruence of the calls-to-action on CB, and whether descriptive social norms mediate the effects of normative information on CB, a mediation analysis will be conducted. This can be done by using the bootstrapping method developed by Preacher and Hayes (Hayes, 2013). This is because previous approaches related to this analysis, such as the causal step approach (Baron and Kenny, 1986), have been criticized for lack of power, the underlying assumptions and inability to directly evaluate potential mediation (MacKinnon et al., 2002).

To determine if people’s moral foundations can be predicted from their Facebook data, various machine learning algorithms can be employed^5^. However, as this part of the study is exploratory and primarily concerned with maximizing prediction accuracy, we cannot specify the exact algorithm which will be reported. Various models and approaches can be tried out, choosing the one that exhibits the least amount of generalization error, i.e., the one that performs best on unseen data, which will be determined through cross-validation. Some possible approaches are LASSO (*Least Absolute Shrinkage and Selection Operator*) regression, multiple linear regression on clustered data and principal component regression^6^ (James et al., 2013; Kosinski et al., 2016).

The analyses can be conducted using the R language (R Core Team, 2017). For implementing the various machine learning algorithms, we will use existing packages, such as glmnet (Friedman et al., 2010), irlba (Baglama et al., 2017) and topicmodels (Grün and Hornik, 2011).

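### Omitting participants without a clear moral profile is justified for the congruence tests but not for the norm main effect, which as written loses them too; the Limitations section implies that they stay in

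*Protocol article*

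**What the plan says.** In the protocol article, the Participants section derives a MANOVA sample size and then raises it by 20% because "it is expected that researchers will have to omit some participants whose scores do not meet the criteria for individualizing and binding groupings". The bracketed reason is that the calls do not match or oppose these people's moral views clearly enough. The section does not say which analyses the omission covers.

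Statistical Analysis names one MANOVA "To test for the effects of moral congruence of the calls-to-action, descriptive social norms, and their interaction on donations of time and money", with the moderation by moral internalization in the same analysis. Mediation is a separate bootstrap analysis. No other test of the norm effect is described.

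Under Stepwise Procedure, the moral foundations questionnaire comes at step 2. At step 4 "the participants are randomly assigned to one of the two different charity causes and to one of six different experimental conditions". Normative Information defines the norm factor simply as a message shown or not shown with the call. Aims and Hypotheses states the norm hypothesis for participants in general.

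Limitations returns to people who fit neither grouping. It says that they will be spread at random over the conditions and may weaken the manipulations. It mentions no omission.

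**The concern.** Whether a call is congruent depends on the reader's moral profile. Without a profile, a participant shown an individualizing or binding call has no congruence level. Leaving such people out of the congruence, congruence × norm and congruence × internalization tests is therefore reasonable.

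The norm factor is different. Everyone is randomised to see the message or not, and that assignment needs no profile. Because the norm effect is tested only inside the model that contains congruence, a restriction meant for one factor also falls on the other.

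Two things are at stake. The norm hypothesis would be tested on fewer people than were randomised and assessed. The effect would also be estimated only in people with a clear individualizing or binding profile, although the hypothesis is not limited to them. The charities that the article hopes to advise also address people such as libertarians, whom Limitations names as not fitting the two groups.

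**Working it through.** **Inputs (Participants section).** "error set at α = 0.05"; "power of at least 1−β = 0.90"; effect size f² = 0.02; "we would need a sample size of *N* = 439", raised by 20% to about 527; for power 0.80, "one would need the sample size of *N* = 344, or around *N* = 412". From the design and analysis sections: p = 2 outcomes (time, money) and k = 6 cells.

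**Formula.** Noncentral F for Pillai's trace, with h the hypothesis degrees of freedom: s = min(p, h), df1 = p·h, df2 = s(N − k − p + s), λ = N·s·f².

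**The plan's own figures.** With p = 2 and h = 3:
- N = 439: λ = 439 × 2 × 0.02 = 17.56, df = (6, 866), power 0.900.
- N = 344: λ = 344 × 2 × 0.02 = 13.76, df = (6, 676), power 0.800.
- Inflation: 439 × 1.2 = 526.8 and 344 × 1.2 = 412.8, in line with the stated 527 and 412.

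Both sample sizes reproduce exactly.

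**Size of the allowance.** (527 − 439)/527 = 88/527 = 16.7%. In the smaller plan, (412 − 344)/412 = 68/412 = 16.5%.

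**Norm main effect.** Here h = 1, so s = 1, df1 = 2, df2 = N − 7 and λ = 0.02·N.

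| N | λ | df2 | Power |
|---|---|---|---|
| 344 | 6.88 | 337 | 0.643 |
| 412 | 8.24 | 405 | 0.728 |
| 439 | 8.78 | 432 | 0.757 |
| 527 | 10.54 | 520 | 0.834 |

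Keeping everyone gains 83.4 − 75.7 = 7.7 points in the main plan and 72.8 − 64.3 = 8.5 points in the smaller one, if the full allowance is used.

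**Sensitivity to the effect size.** A univariate two-group test with equal groups gives the following at N = 439 and N = 527. At an assumed d = 0.20, power is 0.554 and 0.631. At d = 0.28, it is 0.835 and 0.895. At d = 0.58, the norm effect cited under Significance of Research, power already exceeds 0.999 at N = 344, so the loss would be immaterial.

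**The two sections side by side.** Participants says that people who fit neither group will have to be left out. Limitations says that they are distributed over conditions and may dilute the manipulations, a caveat that makes sense only if they are analysed. Neither section says which sample serves the norm test.

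**The case against.** Several points against this have force.

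- **A reason is given.** A reader might infer that people are discarded for no reason. The Participants section does give one, and it is valid for every term that uses congruence. It just does not reach the norm main effect.
- **Omission from every analysis is not stated.** A reader might infer it, but it follows only from reading Participants together with Statistical Analysis, and Limitations points the other way. Norm mediation needs no congruence variable, and nothing restricts its sample. It is affected only if the omission is study-wide.
- **One in six is not an exclusion rate.** The text says some participants and advises a 20% increase. No rate is planned or predicted.
- **Not everyone lacks a level.** Anyone shown the neutral call has a defined level. If only those without a level dropped out and allocation were equal (an assumption), the loss would be about 88 × 2/3 ≈ 59, not 88. The omission as worded, however, goes by scores and not by the call shown.
- **The planned N is protected.** The inflation exists so that 439 remain, so there is no shortfall against the stated target. The distance from 75.7% to 90% is not caused by the omission. It arises because 439 matches a test with h = 3, while the norm effect has h = 1. The omission accounts only for the step from 83.4% to 75.7%.
- **No bias is shown.** A reader might infer a biased norm comparison. The profile is measured before assignment, so restricting on it leaves that comparison randomised.
- **One analysis set for a factorial MANOVA is conventional**, and a second model adds a test. That is a real cost, but a small one.

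**Conclusion.** The point stands in limited form. The stated reason for omission does not cover the norm main effect, yet the only described norm test would inherit the omission. Participants and Limitations also conflict on whether these people are analysed.

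The consequence is lost precision and a narrower population. The power cost is at most about 8 points: 83.4% down to 75.7% in the main plan, 72.8% down to 64.3% in the smaller one. This assumes f² = 0.02, two outcomes, a 1-df test and full use of the allowance. It shrinks with fewer omissions and vanishes at the larger norm effect that the article cites.

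The conclusion that the norm comparison stays unbiased assumes that the grouping is fixed from the moral foundations scores without regard to outcomes. The article leaves the grouping criteria to be determined from the data but does not say that outcomes would be used. How the cut-offs are chosen is a separate matter.

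**What to change.** - Test the norm main effect and the norm mediation in all randomised participants, in a model with the call text as assigned (individualizing, binding or neutral), norm and charity.
- Restrict to classifiable participants only the tests that use congruence: its main effect, congruence × norm and congruence × internalization.
- Reconcile Participants with Limitations on what happens to people who fit neither grouping, and state in Participants which N applies to which hypothesis.

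The cost is one extra model and a few sentences, with no new data or recruitment. The drawback is that different hypotheses would rest on different analysis sets, which the report must make clear.

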## Abstract

Online advertising is an important tool that can be utilized by charities to elicit attention and funding. A critical examination of advertisement strategies is thus necessary to increase the efficacy of fundraising efforts. Previous studies have shown that individuals’ moral views and perceptions of social norms can play important roles in charitable behavior. Thus, the current protocol describes a study to examine whether framing charitable advertisements in line with participants’ morality and increasing the salience of descriptive social norms increases subsequent charitable behavior. We describe experimental, online methods, whereby participants are provided with a framed call-to-action and normative information within a custom-developed application or existing survey platform. Furthermore, in the exploratory fashion, we discuss the possibility of collecting participants’ Facebook data and predicting moral profiles from this data. If there is an increased rate of donations as a result of moral compatibility and/or increased norm salience, charities can leverage this knowledge to increase the donations by tailoring their campaigns in a more appealing way for their prospective donors. Moreover, if it turns out to be possible to predict one’s moral profile from Facebook footprints, charities can use this knowledge to find and target people that are more likely to support their cause. However, this introduces important ethical questions that are discussed within this protocol.

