Therefore, following from the RFT, it can be hypothesized that a person’s attitudes would change if a persuasive message was congruent with his/her moral views. One of the most influential and extensive theories that describe individuals’ moral systems is the Moral Foundations Theory (MFT; Haidt and Joseph, 2004; Haidt and Graham, 2007; Graham et al., 2011, 2012). MFT postulates that five different, innate, moral foundations provide a “first draft” of moral intuitions; but these intuitions can also be revised through exposure to social context and culture (for a detailed review, see Graham et al., 2012). The five moral foundations proposed by MFT are Care/Harm, Fairness/Cheating, Loyalty/Betrayal, Authority/Subversion, and Sanctity/Degradation (Graham et al., 2012). According to the theory, differences in these five foundations are responsible for differences in morality across individuals and cultures.

The first two foundations are called the *individualizing*
*foundations*, meaning that they emphasize inter-individual relations. Individuals scoring highly on these foundations are primarily sensitive to possible cruelty, unfairness, and inequality when making moral judgments (Graham et al., 2012). In contrast, the last three foundations are called the *binding foundations*, which bind individuals into communities. According to the MFT, those scoring highly on these foundations are primarily sensitive to social community, hierarchical relations, and physical and spiritual purity when making moral judgments. Graham et al. (2009) found that politically liberal individuals primarily endorsed and used individualizing moral foundations when making judgments (i.e., Care/Harm and Fairness/Cheating), whereas conservatives endorsed and used all five foundations more equally. These correlational patterns between morality and political ideology have been shown to be stable across cultures (e.g., Bobbio et al., 2011; Graham et al., 2011; Kosugi et al., 2014). This suggests at least two distinct, universal moral foundations profiles: a liberal and a conservative one.

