### Leveraging Social Networks to Foster Charitable Behavior

The percentage of CB conducted online grows every year (e.g., MacLaughlin, 2017). As such, it would be beneficial for charities to take advantage of this and make their online fundraising campaigns more efficient. For example, if charities could target interested potential donors more precisely and approach them with tailored, congruent calls-to-action, this could significantly improve their fundraising outcomes.

One way to target potential donors more precisely is by using big data produced by social networks. When browsing social networks and engaging in behaviors on those networks, people leave digital footprints. Previous research has shown that these footprints can be predictive of different psychological characteristics. Kosinski and his colleagues have conducted multiple studies exploring the potential uses of digital footprints created on social media sites to identify users’ psychological characteristics (e.g., Quercia et al., 2011; Kosinski et al., 2013, 2014; Youyou et al., 2015).^1^

Their research shows that it is possible to predict people’s personality trait scores (e.g., openness and extraversion) based on their digital footprints – specifically, Facebook *likes*. In fact, these predictions can be as accurate as those made by human judges, such as colleagues, friends or spouses (Youyou et al., 2015). Other researchers have demonstrated that it is possible to use social media data to predict various other characteristics. For example, Conover et al. (2011) demonstrated that people’s political alignment can be predicted from their Twitter data with 90.8% accuracy. Furthermore, since an individual’s different psychological properties are reflected in his/her digital footprints, it is possible that these footprints could be used to predict the individual’s moral foundations. If so, it would be possible for charities to directly target people who are more likely to support their cause and become donors, while avoiding those who are less likely to support that specific cause.

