## Aims and Hypotheses

The project has five aims:

(i)to investigate the effect of morally (in)congruent calls-to-action and salient descriptive social norms on CB;(ii)to explore whether these effects occur when the charity’s cause is not aligned with a person’s moral profile;(iii)to examine whether the effects of (in)congruent calls-to-action are moderated by participants’ moral internalization scores;(iv)to investigate whether attitudes toward CB mediate the effect of (in)congruent calls-to-action on CB and whether descriptive social norms mediate the effect of normative information on CB;(v)to investigate whether individuals’ moral foundations can be predicted based on their Facebook behavior.

In previous studies, calls-to-action congruent with one’s moral foundations increased CB (Winterich et al., 2012). Therefore, we hypothesize that morally congruent calls-to-action will have a greater positive impact on CB compared with morally incongruent and neutral calls-to-action, regardless of whether the charity cause itself is in line with one’s moral foundations. Furthermore, we hypothesize that providing participants with normative information, thus making the descriptive norm salient, will significantly affect CB. Additionally, we expect that the impact of morally congruent calls-to-action will be greater in individuals with high moral internalization compared to individuals with low moral internalization. Also, in line with the assumptions of TPB (Ajzen, 1985, 1991), we expect that the effects of calls-to-action congruence on CB will be mediated by attitudes toward CB, and that the effect of normative information on CB will be mediated by the perception of descriptive social norms. Finally, although this part of the research would be purely exploratory, we expect to be able to predict some of the participants’ moral foundations by his/her Facebook behavior. The proposed effects are shown in the Figure 1.

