There are also certain concerns related to using data from social media to predict individual characteristics. For example, Lambiotte and Kosinski (2014) warn that it is possible for companies or individuals to use others’ social media data to infer their personal characteristics (e.g., intelligence or sexual orientation), without them noticing or without their consent. It is especially troublesome that many users may be unaware of how revealing the information available on social media can be (Kosinski et al., 2014). Youyou et al. (2015) point out that personal information can also be used to manipulate or influence people for illicit purposes. Similarly, Matz and Netzer (2017) state that social media data could be used to target individuals who are prone to impulsive or addictive behavior with ads for online casinos. These concerns are real and relevant in today’s digital societies.

However, the outlook does not have to be so bleak. Kosinski et al. (2015) argue that, for instance, Facebook users have far more control over their data than is usually assumed. According to the authors, Facebook requires its users to give consent to applications that want to use their data, and allows them to limit or revoke access to their data after it has been granted. Furthermore, users can be informed of the specific data that is being collected and the way it is being used, allowing them to make an informed decision (Kosinski et al., 2015). Also, once collected, the data can be anonymised and made unrelatable to the specific person prior to conducting analyses. We believe that these, and other steps, can be taken to make the data collection and analysis processes transparent and ethical, safeguarding the participants’ privacy.

Finally, this protocol obtained an official approval from the ethical board of the Department of Psychology, University of Zagreb. Each participant will provide consent for participation and data sharing (just the Facebook likes and no other personal information such as name, residence, friends etc.), will be familiarized with the overall goals of the study and will receive feedback detailing the exact goals of the study as well as the description and explanation of their own scores on the measures.

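### Exploratory aim (v): if recruitment is by ideology, cross-validation inside that sample will tend to overstate how well Facebook likes predict moral foundations in ordinary users

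*Protocol article*

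**What the plan says.** Aim (v) in Aims and Hypotheses is "to investigate whether individuals’ moral foundations can be predicted based on their Facebook behavior". The article labels this part exploratory and optional.

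- **Recruitment (Participants).** To obtain a political mixture, "the link to the survey can be disseminated through different conservatively and liberally oriented Facebook groups". The further options are also chosen by ideology: "Other online platforms where it is relatively easy to approach the users of different ideological positions can be also utilized".
- **Target and ideology (Changing Behavior by Changing Attitudes).** After describing how liberals and conservatives differ on the five foundations, the article states: "These correlational patterns between morality and political ideology have been shown to be stable across cultures". It gives no coefficient.
- **Predictors (Ethics).** The data taken from Facebook are "just the Facebook likes and no other personal information such as name, residence, friends etc".
- **Validation (Statistical Analysis).** Several algorithms may be tried, and the one retained is "the one that performs best on unseen data, which will be determined through cross-validation". No separate test sample is named.
- **Use.** The Abstract says that, should prediction prove possible, "charities can use this knowledge to find and target people that are more likely to support their cause". Leveraging Social Networks to Foster Charitable Behavior says, also conditionally, that "it would be possible for charities to directly target people who are more likely to support their cause".

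The Limitations section covers hypothetical bias, participants who fit neither moral grouping, and access to the app. It does not mention that the prediction sample may be selected by ideology.

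**The concern.** The suggested recruitment selects people on ideology. Ideology is related to the target (the moral foundation scores) and plausibly to the predictors (likes). Drawing people from both political ends widens the spread of ideology and so strengthens the observed association between likes and foundations. A correlation, an R² or a classification rate depends on that spread, so each will tend to be higher here than in a general population of users.

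Cross-validation does not correct this. Random folds put the same recruitment sources in the training and test parts, so the held-out people are new individuals from the same selected population. Performance on them answers a narrower question than the one a charity has when it looks for prospective donors. The problem comes from the sampling and would remain with a single model fixed in advance.

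At stake is the practical message attached to aim (v): an accuracy obtained among politically engaged recruits could be read as the accuracy available for targeting the public.

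**Working it through.** **The plan's own figure.** The article states no prediction accuracy, so there is none to reproduce. Its ideal sample, 439 × 1.20 = 526.8, or 527, was set for the MANOVA. It is used below only as a realistic sample size; those who grant access to their likes could be fewer. All other inputs are assumptions.

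**Step 1. How far recruitment by ideology widens the spread.** Let ideology *I* be standard normal in ordinary users, and let V be its variance in the recruited sample.
- Everyone beyond ±1 SD: V = 1 + φ(1)/(1 − Φ(1)) = 1 + 0.2420/0.1587 = 2.525.
- Half beyond ±1 SD, half unselected: V = 0.5 × 2.525 + 0.5 × 1 = 1.763.

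If a foundation correlates *r* with ideology, its SD rises by √(1 + r²(V − 1)). With everyone beyond ±1 SD:
- r = 0.3: √(1 + 0.09 × 1.525) = 1.07
- r = 0.5: √(1 + 0.25 × 1.525) = 1.18

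**Step 2. Effect on the correlation under indirect selection.** Suppose a like-based score correlates *a* = 0.6 with ideology and relates to the foundation only through it. Then

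ρ(sample) = a·r·V / √{[1 + a²(V − 1)] [1 + r²(V − 1)]}

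For example, r = 0.5 and V = 2.525 give 0.7575/√(1.549 × 1.381) = 0.52.

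| Assumed r | Ordinary users (a × r) | Half beyond ±1 SD | All beyond ±1 SD |
|---|---|---|---|
| 0.3 | 0.18 | 0.27 | 0.34 |
| 0.5 | 0.30 | 0.43 | 0.52 |

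**Step 3. Simulation with actual cross-validation.** Foundation = r·I + √(1 − r²)·noise; 100 binary likes whose log-odds depend on *I*; ridge regression; N = 527; 5 folds; 30 repetitions. The model fitted to the recruited sample was then applied to 2,000 unselected users.

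| Recruited sample | r | Cross-validated correlation | Same model, ordinary users | Gap |
|---|---|---|---|---|
| Half beyond ±0.5 SD | 0.3 | 0.19 | 0.17 | 0.02 |
| Half beyond ±0.5 SD | 0.5 | 0.39 | 0.34 | 0.05 |
| All beyond ±0.5 SD | 0.3 | 0.22 | 0.18 | 0.04 |
| All beyond ±0.5 SD | 0.5 | 0.45 | 0.35 | 0.10 |
| Half beyond ±1 SD | 0.3 | 0.25 | 0.17 | 0.08 |
| Half beyond ±1 SD | 0.5 | 0.48 | 0.35 | 0.13 |
| All beyond ±1 SD | 0.3 | 0.33 | 0.18 | 0.15 |
| All beyond ±1 SD | 0.5 | 0.56 | 0.37 | 0.19 |

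A second set-up (200 likes, 10 folds, everyone beyond ±1 SD) gave 0.30 against 0.15 for r = 0.3, 0.54 against 0.33 for r = 0.5, and 0.72 against 0.51 for r = 0.7.

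**Step 4. Absolute error.** In Step 3 the RMSE was 0.96 to 1.02 by cross-validation and 0.95 to 1.01 in ordinary users. It hardly changes, so the optimism concerns correlation-type and classification measures.

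**The case against.** **The channel is only an example.** True: the wording is permissive, and the app's share-and-invite feature could dilute the selection or reinforce it. The point is therefore conditional on that route. But the other platforms are recommended on the same ground, ease of reaching users of differing ideology, so they do not remove it.

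**A reader might infer that the accuracy is circular.** The document does not support that. The foundations are measured by a 30-item questionnaire, independently of Facebook. Only likes are collected, and nothing says that membership of a recruiting group appears among them.

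**A reader might infer a much larger inflation.** The direct range-enhancement formula R = r·u/√(1 + r²(u² − 1)), with r = 0.30 and the moral score's SD doubled (u = 2), gives R = 0.53, which takes R² from 0.09 to 0.28. That formula is for direct selection on the predictor or target, whereas selection here is on ideology. The SD ratio is also too high. Step 1 gives at most 1.18. Reaching 2 would need ideology's SD to rise 3.6-fold (√13, r = 0.5) or 5.9-fold (√34.3, r = 0.3).

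**Ideology read from likes is real signal.** This stands. Significance of Research expects charities to use approximate ideological position, so making within-ideology accuracy the headline would answer a different question.

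**The part is exploratory, its claims are conditional, and cross-validation is a standard way to choose a model.** All true, and this limits the weight of the point. The label excuses leaving the algorithm open. It does not extend accuracy from a politically selected sample to prospective donors in general, which is the use that the Abstract describes.

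**Conclusion.** The point holds as selection (spectrum) bias, confined to optional aim (v) and conditional on recruitment by ideology. In that case cross-validated correlation, R² or classification accuracy will tend to overstate performance among ordinary users, and random folds cannot show it. RMSE is not clearly affected.

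The direction follows from the article's own statements on recruitment and ideology, together with the plausible assumption that likes reflect ideology. The size does not: the article gives neither the ideology-foundation correlation nor the degree of political enrichment. Under the assumed inputs the simulated correlation gap runs from about 0.02 with mild enrichment to about 0.2 when the whole sample lies beyond ±1 SD. The simulations let likes relate to foundations only through ideology; if likes carry further information, the gap could differ.

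No randomised comparison, hypothesis test or sample size is affected. The point is minor.

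**What to change.** 1. Use a separate survey link for each recruitment channel so that source is recorded. This costs almost nothing before launch, and source cannot be reliably recovered afterwards.
2. Report accuracy from source-grouped (leave-one-source-out) folds beside the pooled cross-validated figure.
3. Report accuracy within levels of self-reported ideology, which the demographic questions already collect, as a secondary result and not as the headline.
4. In the Abstract and in Leveraging Social Networks to Foster Charitable Behavior, limit the targeting claim to the population sampled, unless the model is also tested in a sample not recruited by ideology. Add the selection to Limitations.

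Item 4 is needed as well as item 2: grouped folds reduce source-specific leakage, but every source may still be politically selected, so they do not undo the polarised sampling.

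The cost is a tag in each link, a different fold assignment and a few sentences. The downside is a lower and noisier reported accuracy. A test sample not recruited by ideology would be the stronger remedy, at the price of extra recruitment.
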